# Multimodal prehabilitation for major surgery in elderly patients to lower complications: protocol of a randomised, prospective, multicentre, multidisciplinary trial (PREHABIL Trial)

**DOI:** 10.1136/bmjopen-2022-070253

**Published:** 2023-01-03

**Keywords:** surgery, clinical trials, geriatric medicine

## Abstract

**Introduction:**

The global volume of surgery is growing and the population ageing, and economic pressure is rising. Major surgery is associated with relevant morbidity and mortality. Postoperative reduction in physiological and functional capacity is especially marked in the elderly, multimorbid patient with low fitness level, sarcopenia and malnutrition. Interventions aiming to optimise the patient prior to surgery (prehabilitation) may reduce postoperative complications and consequently reduce health costs.

**Methods and analysis:**

This is a multicentre, multidisciplinary, prospective, 2-arm parallel-group, randomised, controlled trial with blinded outcome assessment. Primary outcome is the Comprehensive Complications Index at 30 days. Within 3 years, we aim to include 2×233 patients with a proven fitness deficit undergoing major surgery to be randomised using a computer-generated random numbers and a minimisation technique. The study intervention consists of a structured, multimodal, multidisciplinary prehabilitation programme over 2–4 weeks addressing deficits in physical fitness and nutrition, diabetes control, correction of anaemia and smoking cessation versus standard of care.

**Ethics and dissemination:**

The PREHABIL trial has been approved by the responsible ethics committee (Kantonale Ethikkomission Bern, project ID 2020-01690). All participants provide written informed consent prior to participation. Participant recruitment began in February 2022 (10 and 8 patients analysed at time of submission), with anticipated completion in 2025. Publication of the results in peer-reviewed scientific journals are expected in late 2025.

**Trial registration number:**

NCT04461301.

STRENGTHS AND LIMITATIONS OF THIS STUDYThis study focuses on frail, elderly patients undergoing major surgery with a proven low functional capacity using cardiopulmonary exercise testing.It implements a structured, multidisciplinary, multimodal prehabilitation intervention addressing low functional capacity, malnutrition, anaemia and smoking.The primary endpoint is the Comprehensive Complication Index at 30 days.Patient-reported outcomes such as Quality of Recovery are implemented as secondary outcomes.The study is not blinded due to the nature of the intervention, however, primary outcome is assessed by a blinded adjudication committee.

## Introduction

### Background

The global volume of surgery has grown by about a third, from 234 million procedures in 2008 to more than 312 million in 2012, with most surgeries being performed in developed countries.^1 2^ Mortality rates are estimated to be between 1% and 4% in Europe.^3^ A minority of patients at high risk seem responsible for the majority of complications and mortality.^4^ It is, therefore, of key importance to identify patients at risk preoperatively for several reasons: it allows informed decision-making, it offers the opportunity for preoperative optimisation and it identifies patients with increased intraoperative and postoperative monitoring needs.

### Risk prediction before major surgery

Perioperative risk is largely determined by three domains: urgency of surgery, surgery-specific risk factors such as invasiveness, expected blood loss or fluid shifts, and patient-specific risks such as age, comorbidities and fitness. Whereas the first domain is usually non-modifiable, the latter two are modifiable to some extent, offering the opportunity to adjust the surgical procedure or optimise the patient’s condition prior to surgery.

Several preoperative or perioperative risk scores and prediction models have been proposed and validated, such as the Portsmouth Physiological and Operative Severity Score for the enumeration of Mortality and morbidity (P-)POSSUM, Surgical Risk Score, the American College of Surgeons National Surgical Quality Improvement Programme or the Preoperative Score to Predict Postoperative Mortality for non-cardiac surgery (NCS) or the European System for Cardiac Operative Risk (EuroScore) for cardiac surgery.^5–9^ In addition, organ-specific risk scores such as Revised Cardiac Risk Index for cardiac complications and many others have been published and widely used.^10 11^

Traditionally, patients’ reported health state, medical history and clinical assessment were used to classify the patients’ individual risk, for example, using the American Society of Anesthesiologists^12^ score. Accordingly, level of fitness was reported by the patients themselves. Based on the 2022 European Society of Cardiology/European Society of Anaesthesiology (ESC/ESA) guidelines, for example, further investigations such as (cardiac) stress testing are indicated for patients with low functional capacity (less than four metabolic equivalents of task) before high-risk elective NCS and high likelihood or proven coronary artery disease or before intermediate-risk NCS when ischaemia is of concern in patients with clinical risk factors and poor functional capacity.^13^

Patient-reported measures of functional capacity remain notoriously unreliable. Better performance was seen when using the Duke Activity Status Index (DASI) questionnaire, which correlated well with objective, cardiopulmonary exercise testing (CPET)-derived parameters such as peak oxygen consumption (VO2_peak_) and was able to predict cardiovascular events in a recent trial.^14^ While CPET remains the gold standard for global assessment of functional capacity, it is laborious for the patient and costly. Therefore, the Canadian Cardiovascular Society recommends against performing perioperative CPET to enhance cardiac risk estimation.^15^ Nevertheless, an anaerobic threshold (AT) level of <11 mL/kg/min has been confirmed as a reliable predictor for increased perioperative risk.^16 17^ This also applies to the elderly patient.^18^ In addition, the AT has the better discriminatory power to identify patients with reduced functional capacity comparted to the 6 min walking test (6MWT), which is recommended for departments lacking CPET equipment.^19^ Very recent evidence found that an increased VE/VCO2 slope might be an even more sophisticated prognostic marker to predict morbidity in high-risk patients having major cancer surgery or patients undergoing lobectomy for lung cancer.^20 21^

With increasing age, the physiological resilience to external stressors such as surgery diminishes, while the number of comorbidities rises and muscle mass decreases. In addition, elderly people are often malnourished, have a weakened immune system and impaired wound healing. All these factors contribute to a reduction in functional capacity.^22^ Despite the inconsistency of the definition of frailty, it can be assessed using a variety of tools such as the clinical frailty scale or more objective Fried frailty criteria including gait speed and handgrip strength, which are useful predictors of all-cause mortality and cardiovascular disease and death in elderly surgical and non-surgical patients.^23–25^ Similarly, standardised screening and assessments exist for the diagnosis of malnutrition and sarcopenia, which demonstrated significant overlap with frailty.^26–28^ In summary, the elderly, frail, malnourished and sarcopenic patient is especially at risk for perioperative complications, however, many options for medical, physiological and psychological optimisation exist.^29^

### Interventions to reduce perioperative risk

Organ specific, medically mandated interventions (as brought up by the preoperative assessment, such as treatment of relevant aortic or coronary stenosis) have to be completed prior to major surgery, irrespective of any study participation. However, despite clear guidelines on patient blood management, for example, relevant anaemia is not always corrected. In fact, less than half of Swiss hospitals had implemented a patient blood management programme in the year 2022.^30^

To empower the patient physically and psychologically to withstand the stress of surgery and to hasten recovery, the focus is widening from the intraoperative and postoperative to the perioperative period as a continuum. In addition, patients are believed to be more receptive for beneficial changes in behaviour prior to surgery than during the phase of recovery. Whereas rehabilitation is covering the postoperative period, the term prehabilitation has emerged for interventions occurring weeks before surgery.

As of today, prehabilitation is a complex approach with a combination of possible interventions (e.g., exercise, nutrition, psychosocial, and medical optimisation), and there is no precise definition of the type of intervention, the optimal dose nor duration required. This has led to widely differing interpretations and protocols of interventional trials with unimodal (addressing only one domain such as physical fitness, whereby also mixed-exercise programmes including aerobic, resistance and inspiratory muscles training were implemented) or multimodal (addressing additional domains such as anaemia, malnutrition, smoking behaviour and psychological support) interventions.

Many conflicting results for clinical effectiveness of prehabilitation interventions have been reported.^31–34^ The potential for cost reduction seems plausible, but good evidence from randomised controlled trials is lacking so far.^35–38^

Potential reasons for these equivocal results are several fold, with the first and most important probably being inappropriate patient selection. From eight randomised trials addressing prehabilitation before major intra-abdominal cancer surgery, only two limited the study population to ‘high-risk’ patients, based on age, American Society of Anaesthesiologists or Dukes classification, however, none of them used objectively measured physical fitness as an inclusion criteria.^39^ Selecting patients with a relatively low risk for perioperative complications will inevitably lead to a dilution of the possible positive effects and produce negative results regardless of the intervention or surgeries studied. The small or inexistent benefit to ‘low-risk’ patients does not warrant the time-demanding and resource-demanding interventions. In addition, the time required for the intervention has been found to make recruitment of large cohorts difficult.^40 41^

Second, poor results may have been due to implementing unimodal rather than individually tailored multimodal interventions that cover all domains of patients’ health state prior to surgery, such as physical fitness, malnutrition, diabetes control, anaemia, smoking and psychological well-being.

Insufficient exercise capacity is believed to be the most important predictor for postoperative complications,^42^ and therefore, mandates careful assessment with appropriate patient selection. While physical fitness interventions (even high-intensity/interval training) have been proven to be safe and feasible and have led to a measurably increased fitness levels (e.g., 6MWT), they failed to produce outcome benefits, possibly due to inappropriate patient selection, unimodality (e.g., lack of considerations of other factors such as malnutrition) and adherence.^43–46^

Further, up to one-third of surgical patients are malnourished, and malnutrition has been proven to be associated with increased morbidity, mortality and cost.^47 48^ For malnourished patients, oral nutritional supplementation, in particular adequate protein supplementation, was shown to be effective in improving outcomes.^49–51^ Malnutrition is often associated with sarcopenia and frailty, making a combined intervention of exercise training and nutritional support promising.^22 45 52^ However, so far, nutritional assessment and intervention have been poorly standardised, making conclusions regarding its efficacy and interstudy comparisons difficult.^53^

A further frequent metabolic comorbidity is diabetes affecting approximately 30%–40% of people undergoing elective surgery. Surgical outcomes are worse in people with diabetes with an up to three-fold higher risk of postoperative complications including poor healing, wound complications and renal dysfunction. Although inadequate glucose control was associated with poor surgical outcomes,^54^ no systematic strategies to improve diabetes management prior to surgery are currently recommended and only few prehabilitation programmes included diabetes optimisation as part of a multimodal concept.

Anaemia-related perioperative blood transfusions and smoking have both been found to be related to worse outcomes and increased costs.^55–57^

The negative influence of preoperative anxiety or depression on postoperative outcomes such as quality of life has gained more attention.^58 59^ Even without an proper psychosocial intervention, physical exercise can reduce psychological distress in addition to improving cardiovascular function and ultimately improve wound healing.^60^

Another factor contributing to negative results of existing multimodal prehabilitation programmes might be attributable to the simple fact that patients were randomised into the intervention group, but were not taking actively part in the programme (lack of patient adherence).^61^ Some studies fail to demonstrate this effect by not measuring adherence rates at all^12^

So the necessity of implementing a multimodal intervention seems obvious given the important contribution of anaemia, smoking, nutritional status, physical fitness and psychological well-being. Nevertheless, even for multimodal prehabilitation, the level of evidence remains low and conflicting, with inappropriate patient selection appearing to be the main reason.^32 33^

In conclusion, no trials to date have limited the study population to ‘high-risk’ patients most prone to benefit from prehabilitation. Further, only few studies have implemented a multimodal approach targeting correction of anaemia and malnutrition, smoking cessation and improving physical fitness. There is a need for trials with stringent selection of the patients who will benefit most from preoperative optimisation and implementation of personalised comorbidity mitigation and risk factor management offered in the form of individually tailored multimodal prehabilitation.^62^

### Outcome measures after major surgery

The most widely accepted postoperative hard outcome measure is mortality at 30 days.^6^ Nevertheless, extending the follow-up to at least 90 days or ideally 1 year has been proposed.^63^ To grade postoperative complications, the Clavien-Dindo classification has been established and recommended by the ESA-European Society of Intensive Care Medicine joint taskforce on perioperative outcome measures.^63–65^ There is a huge variety of possible postoperative complications, and powering studies for individual complications is nearly impossible. To overcome this difficulty, the Comprehensive Complication Index (CCI) has been developed.^66^ It is a continuous scale to measure surgical morbidity (ranging from 0=no complications to 100=death) and can be used to reduce sample size in randomised controlled trials as it provides a more sensitive endpoint.^67–69^

### Calculation of cost savings

The CCI can be used to calculate costs, as postoperative morbidity correlates highly with healthcare costs. Staiger *et al* found a 14% increase to the baseline cost for each 10-point increase in CCI.^70^ Therefore, a CCI reduction can serve as a surrogate marker for cost savings.

### Study hypothesis

We hypothesise that the implementation of a multimodal, multidisciplinary prehabilitation programme over 2–4 weeks, consisting of physical exercise, nutrition, anaemia correction and smoking cessation, will result in lower CCI within 30 days after major surgery in elderly patients.

### Feasibility: preliminary data

After ethics approval and logistic preparations, we were able to include 18 patients from March 2022 to October 2022 (table 1).

**Table 1 T1:** Preliminary results

	Control group (n=8)	Intervention group (n=10)
Demographics/comorbidities		
Age (years)	78.25 (SD 5.4)	78.20 (SD 5.5)
Female sex	2 (25%)	1 (10%)
ASA score=III (n)	2 (25%)	2 (20%)
ASA score ≥IV (n)	6 (75%)	8 (80%)
Fried Frailty Scale (n)	1.9 (SD 1.1)	2.1 (SD 1.2)
Smoking (y/n)	1 (12.5%)	0 (0%)
Anaemia (y/n)	2 (25%)	4 (40%)
Nutritional deficit (NRS-2002≥3) (y/n)	2 (25%)	1 (10%)
Ischaemic heart disease or chronic heart failure (y/n)	4 (50%)	6 (60%)
Diabetes (y/n)	3 (37.5%)	3 (30%)
Obesity (BMI ≥30 kg/m^2^) (y/n)	1 (12.5%)	1 (10%)
Surgical procedure		
Cardiac	2	3
Orthopaedic	0	1
Thoracic	0	1
Urologic	3	4
Vascular	2	1
Visceral	1	0
Use of ECC (y/n)	2 (25%)	3 (30%)
P-POSSUM (baseline)	43.3 (SD 6.5)	45.2 (SD 8.2)
Days to surgery (days)	29.8 (SD 19.7)	28.5 (SD 9.3)
Laboratory parameters (baseline)		
Haemoglobin (g/L)	136.8 (SD 16.3)	126.9 (SD 13.8)
NT-proBNP (pg/mL)	3677.4 (SD 5022.3)	886.8 (SD 881.5)
Albumin (g/L)	33.3 (SD 3.9)	36.0 (SD 2.3)
Prealbumin (g/L)	0.22 (SD 0.04)	0.25 (SD 0.06)
HbA1c (%)	6.0 (SD 0.7)	6.4 (SD 1.4)
Creatinine (mmol/L)	147.9 (SD 51.5)	131.0 (SD 53.4)
Fitness		
MIP (cmH20)	51.3 (SD 28.0)	46.9 (SD 16.1)
AT (mL/min/kg)	9.8 (SD 1.0)	9.1 (SD 1.3)
VO2peak (mL/min/kg)	12.7 (SD 1.4)	11.8 (SD 2.8)
Questionnaires		
STAI (n)	10.6 (SD 2.4)	13 (SD3.9)
DASI (n)	4.1 (SD 0.8)	4.6 (SD 1.4)

ASA, American Society of Anesthesiologists; AT, anaerobic threshold; BMI, body mass index; DASI, Duke Activity Status Index; ECC, extracorporeal circulation; HbA1c, glycated haemoglobin; MIP, maximum inspiratory pressure; NRS-2002, Nutritional Risk Screening 2002; NT-proBNP, N-terminal-pro hormone brain-derived natriuretic peptide; STAI, state-trait anxiety inventory.

## Methods

### Study design

This is a national multicentre, multidisciplinary, prospective, two-arm parallel-group, randomised, controlled superiority trial with blinded outcome assessment. We aim to include 466 patients within 3 years. The present protocol complies with the Standard Protocol Items: Recommendations for Interventional Trials (SPIRIT) 2013 guidelines, defining standard protocol items for clinical trials.

### Participants and enrolment

Surgeons scheduling the operation will prescreen the patients for frailty based on the clinical frailty scale.^71^ This tool is easy to implement in clinical practice, especially when compared with other, more sophisticated scales.^72^ If the patient achieves at least four points on the clinical frailty scale (living with very mild frailty) and there is sufficient time for prehabilitation (at least 2 weeks), informed consent will be sought, followed by a screening CPET (baseline visit, see figure 1).

**Figure 1 F1:**
[figure not shown]
Study flow chart. CFS, Clinical Frailty Scale; CPET, cardiopulmonary exercise testing.

### Inclusion criteria

Participants are eligible if aged 65 years or over, have planned major visceral, urologic, cardiac, vascular, orthopaedic or thoracic surgery, are classified as ASA III or higher by the attending anaesthetist, and have a proven deficit in functional capacity measured during the screening CPET defined as follows:

VO2 at AT <11 mL/kg/min or peak VO2 <14 mL/kg/min on cycle ergometer.VO2 at AT <13 mL/kg/min or peak VO2 <16.5 mL/kg/min on treadmill.VO2 at AT <9 mL/kg/min or peak VO2 <11.3 mL/kg/min with arm crank.VE/VCO2 slope ≥33 (independent of modality).

Patients with VO2 above thresholds during the screening CPET will nevertheless be consented, in order to collect their CCI at 30 days. CCI at 30 days will be compared descriptively between patients qualifying and not qualifying for this study for qualitative clinical assessment outside the purpose of this study.

### Exclusion criteria

Patients are excluded if scheduled for emergency surgery, if unable to exercise for physiological or psychological reasons, if having cognitive disabilities making adherence to interventions impossible or if requiring dialysis due to logistic reasons.

### Preoperative assessments

All patients are assessed twice during the preoperative phase, once at inclusion (baseline) and once the day before surgery (preoperative). Measurements conducted during these visits include CPET, grip strength and maximal inspiratory pressure for the assessment of physical fitness. Bioelectrical impedance analysis^13^ measurements and validated nutritional screening and assessment tools (Nutrition Risk Screening 2002 (NRS-2002) and the Subjective Global Assessment [SGA]) will be performed to quantify participants’ body composition and nutritional status. Blood samples are taken to screen for anaemia (haemoglobin, reticulocyte index, renal function, iron status using transferrin saturation), nutritional and diabetic status (albumin, prealbumin, glucose, glycated haemoglobin (HbA1c)), micronutrient deficits (erythrocyte folate, holotranscobalamin, 25-hydroxy-vitamin D) and cardiac function (N-terminal-pro hormone brain-derived natriuretic peptide (NT-proBNP), high-sensitivity (hs) TroponinT). For smokers, exhaled carbon monoxide (CO) is measured (Smokerlyzer Bedfont Scientific, Kent, UK) and smoking habits evaluated by questionnaire including the Fagerström test. All patients are asked to fill in the short form of the State-Trait Anxiety Inventory,^70^ the DASI and (on the day prior to operation) the Quality of Recovery (QoR-)15 questionnaire. An activity tracker (AX3, Axivity, Newcastle, UK) is provided at the screening visit and continuously worn until the preoperative visit, when it is collected from the patient.

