### Group allocation (minimisation)

After completion of the screening visit (CPET), patients who fulfil the inclusion criteria are randomised using computer-generated random numbers, into either intervention or control group. For group allocation, a probabilistic minimisation procedure is used to achieve balanced groups in regard to parameters known to be relevant for outcome after major surgery. We have included the following parameters in the minimisation algorithm (SecuTrial, V.6.1.1.10): type of surgery (visceral, urologic, cardiovascular, orthopaedic, thoracic), smoking, presence of anaemia (haemoglobin below 120 g/L in females, <130 g/L in males), nutritional deficit (NRS ≥3), age group (65–74, 75–84, 85+), ischaemic heart disease or heart failure, known diabetes, sex, obesity (body mass index (BMI) >30 kg/m^2^) and use of extracorporeal circulation.

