### Secondary endpoints

Secondary outcomes are measured before prehabilitation (screening visit) and thereafter (preoperative visit) and at 30 days after surgery (postoperative visit) unless otherwise specified:

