#### Patient-reported outcomes

QoR-15.State-Trait Anxiety Inventory.^70^DASI.

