### Statistical analysis

Data will be analysed on an intention-to-treat basis (primary outcome). Primary and secondary outcomes for the intervention and control groups will be compared.

Primary outcome: We expect that CCI will be skewed, so we will describe CCI as the median plus first and third quartiles. To test the hypothesis (H0) that the study arms result in similar CCIs (in other words, prehabilitation does not prevent postoperative complications), we will use a generalised linear model that can account for skewed data and zero inflation. The model will be adjusted for the minimisation factors used at randomisation. If no adequate model can be fit, the non-parametric Mann-Whitney U test will be used.

Secondary outcomes: All secondary outcomes will be described as means plus SD or median plus first and third quartiles for continuous data as appropriate. Categorical parameters will be described as frequencies plus percentage per time point. To account for repeat measurements of patients, we will use generalised linear mixed models to test the hypothesis of both study arms being equal in terms of secondary outcomes over time. Models will be adjusted for minimisation factors as well as baseline values (before randomisation) of the respective outcome.

Data distribution will be assessed by visual inspection of Q-Q plots.

As a secondary analysis, we will perform a PP analysis. Since the time between randomisation and surgery might differ between the two randomisation groups, we will additionally adjust generalised linear models of the primary outcome for this factor in a sensitivity analysis. Further, we will analyse the impact of adherence to the interventions to the primary outcome.

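### QoR-15 is scheduled only after randomisation, so the secondary-outcome model, which adjusts for each outcome's pre-randomisation value, cannot be fitted to it as specified

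*Protocol article*

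**What the plan says.** The protocol article defines two assessments before surgery, "once at inclusion (baseline) and once the day before surgery (preoperative" (Preoperative assessments). In the same section the anxiety inventory and the DASI are listed without a time restriction, but QoR-15 carries one: "on the day prior to operation) the Quality of Recovery (QoR-)15 questionnaire". The section on postoperative assessment repeats the preoperative set at 30 days and omits only micronutrient and iron status, so QoR-15 is measured again then.

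On allocation: "After completion of the screening visit (CPET), patients who fulfil the inclusion criteria are randomised" (Group allocation). The intervention that follows is a "multimodal, multidisciplinary prehabilitation programme over 2–4 weeks" (Study hypothesis).

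The Secondary endpoints section opens with a default schedule: "Secondary outcomes are measured before prehabilitation (screening visit) and thereafter (preoperative visit", then 30 days after surgery. The sentence allows for exceptions stated elsewhere. The list of patient-reported outcomes begins "QoR-15.State-Trait Anxiety Inventory" and gives no timing exception for QoR-15.

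For repeated secondary outcomes, Statistical analysis specifies generalised linear mixed models and adds: "Models will be adjusted for minimisation factors as well as baseline values (before randomisation) of the respective outcome". The strengths and limitations box states: "Patient-reported outcomes such as Quality of Recovery are implemented as secondary outcomes".

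**The concern.** The schedule and the model do not fit together. The model asks for a QoR-15 value from before randomisation, and the section that sets the timing of the questionnaires provides none. The analyst would have to depart from the stated model for this outcome, and the article does not say how.

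At stake is the precision of the arm comparison on one of three listed patient-reported outcomes, and the clarity of a pre-specified analysis. A later statistical analysis plan could reword the model, but it could not recover a baseline score that was never collected. That is why the point belongs at protocol level.

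**Working it through.** The article gives no effect size, SD, correlation or power for QoR-15, so there is no figure to reproduce. The check is mainly one of timing.

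**Step 1: order of events.**

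| Event | Position relative to randomisation | QoR-15 planned? |
|---|---|---|
| Screening (baseline) visit | before | not under Preoperative assessments; yes if the Secondary endpoints default governs |
| Randomisation | – | – |
| Prehabilitation or standard care, 2–4 weeks | after | – |
| Day before surgery | after | yes |
| 30 days after surgery | after | yes |

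**Step 2: what the model needs.** The covariates are the minimisation factors plus the pre-randomisation value of the same outcome. For QoR-15 the second is missing on the Preoperative assessments schedule.

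**Step 3: the two readings.**
- *Preoperative assessments governs* (the specific statement, allowed by the exception clause under Secondary endpoints). No pre-randomisation score exists and the stated model cannot be fitted.
- *The Secondary endpoints default governs.* A screening score exists, but Preoperative assessments then states the timing wrongly.

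The first reading is the more natural one, because the time restriction is attached to QoR-15 alone among the three questionnaires. Table 1 fits it: it reports the anxiety inventory and the DASI under questionnaires and no QoR-15. A summary table is not proof.

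**Step 4: what a baseline would be worth.** Let rho be the within-arm correlation between baseline and 30-day QoR-15 (assumed). Compared with an analysis without covariates, the variance of the arm difference is multiplied by 1 − rho², and the equivalent gain in sample size is 1/(1 − rho²).

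| rho (assumed) | 1 − rho² | Variance reduction | Equivalent sample size |
|---|---|---|---|
| 0.3 | 0.91 | 9% | × 1.10 |
| 0.5 | 0.75 | 25% | × 1.33 |
| 0.7 | 0.51 | 49% | × 1.96 |

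The plan already adjusts for ten minimisation factors. The further gain is then governed by the partial correlation given those factors. To the extent that they carry the same information as baseline QoR-15, the gain is below the tabled value. At rho = 0.5, 25% is therefore best read as an upper figure.

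**Step 5: how many patients could still have a baseline.** The article reports 18 patients included out of a target of 466: 466 − 18 = 448, and 448/466 = 96%. The share falls as recruitment proceeds.

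**The case against.** The strongest reply is that little is broken. Where no pre-randomisation value exists, the term simply drops out. A mixed model with arm, time and the minimisation factors, taking the preoperative and 30-day scores as outcomes, can be fitted and is unbiased by randomisation. Not measuring a patient-reported outcome at baseline is a legitimate design choice, and the plan nowhere claims a precision gain from baseline adjustment. All of this stands. It limits the point to a model that cannot be fitted *as specified* and to lost precision.

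A reader might infer more: that the plan would use the day-before-surgery score as the baseline and so adjust away part of the effect. If that were done, the 30-day estimate would be reduced by rho × D, where D is the arm difference already present before surgery. With an assumed true effect of 0.30 SD, rho = 0.5 and D = 0.2 SD, the expected estimate is 0.30 − 0.5 × 0.2 = 0.20 SD (simulation of 400,000 patients: 0.202). Over rho 0.3–0.7 and D 0.1–0.3 SD it runs from 0.27 down to 0.09 SD. The documents do not support this inference. The covariate is expressly a value from before randomisation, which the preoperative score is not, and nothing proposes the substitution. It is a hazard to rule out, not a defect of the plan.

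A reader might also extend the point to outcomes recorded once, such as length of stay or days nil per mouth. The mixed models are introduced to handle repeated measurements, and the model for each single-occasion outcome is detail that an analysis plan commonly settles. That extension does not hold as a finding.

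**Conclusion.** The inconsistency is real and confined to QoR-15. Either no pre-randomisation score is planned and the specified adjustment is impossible, or the article gives two conflicting schedules. Validity is not threatened under the plan's own wording. The cost is precision on one secondary outcome: up to about 25% lower variance forgone if the correlation is 0.5, and less where the minimisation factors overlap with baseline QoR-15. The correlation is an assumption; the article gives none. The primary outcome (CCI at 30 days), its model and the sample size are untouched. The correction is worth making because it is cheap, and because a missed baseline cannot be collected later.

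**What to change.** **Preferred.** Add QoR-15 to the questionnaires completed at the baseline visit, before randomisation. Correct Preoperative assessments so that it agrees with Secondary endpoints. Adjust the QoR-15 model for that score, with a missing indicator for patients enrolled before the change; their missing value depends on enrolment date, not on arm. The cost is one short questionnaire at a visit where two others are already completed, plus a protocol amendment.

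**Otherwise.** State under Statistical analysis that QoR-15 has no pre-randomisation value and is modelled with the minimisation factors only; that the preoperative and 30-day scores are both outcomes; and that the preoperative score is never used as the baseline covariate. Add to the list of patient-reported outcomes that QoR-15 is not measured at screening. This costs a wording change only, and forgoes the precision gain.
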